### Blinding

In this RCT procedure, the patients, data collection staff, and data analysts will be blinded. However, the acupuncturist knows the treatment allocation due to the nature of the acupuncture manipulation. During the intervention, the acupuncturist and the data collection researcher will be separated immediately after the treatment starts and are instructed not to exchange information. Data collection staff and data analysts have no information about grouping or treatment.

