### Interventions

All EA treatments will be performed by one acupuncturist who has more than 10 years of experience and a Chinese medicine practitioner license. The treatments will be performed according to the standard protocol already prepared. All participants will take a supine position on the treatment couch to receive treatment. Each participant will receive 14 sessions of treatments, twice a week for 7 weeks. Each session will last for 30 min. No additional treatment is allowed.

All selected patients will be randomized to four groups: group A will receive EA at homotopic acupoints with noxious current intensity, which will be 30% above the patient’s pain threshold. Group B will receive EA at homotopic acupoints with innocuous current intensity, which will be 30% below the patient’s pain threshold. Group C will receive EA at heterotopic acupoints with noxious current intensity. Group D will receive EA at heterotopic acupoints with innocuous current intensity. Thus, group A is called the homotopic noxious group, group B is called the homotopic innocuous group, group C is called the heterotopic noxious group, and group D is called the heterotopic innocuous group. We selected the homotopic acupoints ST25 (Tianshu) and ST26 (Wailing), and the heterotopic acupoints ST36 (Zusanli) and ST37 (Shangjuxu), because these acupoints are most commonly used to treat IBS in China [20].

After local area disinfection, sterile, disposable needles (length 50 mm, diameter 0.30 mm; Huatuo, Suzhou Medical Supply Factory Co., Ltd., Suzhou, China) will be inserted to a depth of 25–40 mm. The acupuncturist will manipulate the needle to achieve a “De-qi” sensation for the patient. ST25 will be connected to the same-side ST26 in group A and group B. ST36 will be connected to the same-side ST37 in group C and group D. The reason behind the connection is to form a circuit containing a HANS-200E stimulator (Nanjing Jisheng Co., China) for 30 min. The frequency in all four groups will be the same as an alternating wave with a frequency of 2/100 Hz. The treatment details for the four groups are presented in Table 1.

**Table 1 Tab1:** Details of treatment in the four groups

Group	Points	Stimulation parameters
Group A	Tianshu (ST25) Wailing (ST26)	Current intensity is 30% above the patient’s pain threshold. Alternating wave with a frequency of 2/100 Hz

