##### 2.6.2.2. Pain threshold (PT)

PT is a secondary outcome in this study, and is a more objective measure of pain than the VAS. The PT will be tested by a digital algometer (EP601C, East China Normal University of Science and Technology, Guangxi, China) immediately before and after each treatment. The most obviously tender point (Ashi point) on the abdomen will be tested. The patient will lie in a supine position on the treatment couch. The algometer has a 1-cm^2^ rubber probe, which will be pressed vertically against the abdominal wall. The trained assessor will position the algometer perpendicular to the tender point and apply gradual pressure at a steady rate of approximately 0.5 kg/cm^2^/s. The patient will request the treatment to be stopped when the applied pressure becomes painful, and the value on the digital algometer will be recorded. The pressure pain threshold will be measured three times at each point, with the average value collected for analysis.

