### 2.10. Quality control

To guarantee the quality of this study, we will run several simulations with our colleagues playing the role of patients to identify any problems with our study protocol before the study begins. The one researcher who tests the PT will be trained many times to improve consistency of results. To guarantee the objectivity of the data, effect assessment and statistics will be blinded during the study period. Finally, all details will be recorded on a patient case report form (CRF).

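### Blinding of the pain-threshold assessor to needling location is not secured, and post-session readings carry local needling effects in groups A and B only

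*Protocol article*

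**What the plan says.** Blinding in the protocol article asserts that "Data collection staff and data analysts have no information about grouping or treatment". The safeguard offered for this is that "the acupuncturist and the data collection researcher will be separated immediately after the treatment starts" and that the two are told not to exchange information. Section 2.10, Quality control, repeats the assurance: "effect assessment and statistics will be blinded during the study period".

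Section 2.6.2.2 has PT measured "immediately before and after each treatment". On the site it says: "The most obviously tender point (Ashi point) on the abdomen will be tested". On the method: "The algometer has a 1-cm^2^ rubber probe, which will be pressed vertically against the abdominal wall". Pressure is raised by hand at roughly 0.5 kg/cm² per second until the patient reports pain. Section 2.10 gives the task to a single person: "The one researcher who tests the PT will be trained many times to improve consistency of results". PT is a secondary outcome, which the article presents as more objective than the VAS.

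Interventions places the needles. For the homotopic groups, "ST25 will be connected to the same-side ST26 in group A and group B"; groups C and D are needled at ST36 and ST37. The abstract identifies the first pair as abdominal and the second as lower limb. Insertion is 25–40 mm deep, followed by manipulation and 30 minutes of current.

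**The concern.** The separation rule takes effect at or after the moment it should guard against. Once treatment has begun, the location of the needles has been settled and may be visible. Someone still present at that point can learn whether the patient is in A/B or C/D.

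A second problem does not depend on who is in the room. The region tested for PT is the region just treated in two of the four groups and an untouched region in the other two. Marks, soreness or numbness from needling can therefore differ systematically between the homotopic and heterotopic groups.

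That is the contrast on which the Discussion states a directional hypothesis, namely that homotopic points will do better. An outcome offered as the more objective measure of pain would be least secure in the comparison that matters most. The pressure is applied by hand and one person takes every reading, so knowledge of location could influence it.

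**Working it through.** The article gives no figure to reproduce on this point. The check consists of setting its statements side by side, plus a count of readings.

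**Step 1: who could know the location, and when.**
- Blinding claims that data collectors know nothing of the allocation.
- Blinding also parts the data collector from the acupuncturist only after treatment has started.
- Interventions makes the needle site differ between A/B (abdomen) and C/D (leg).
- Following the text literally, the data collector may still be present when the site becomes apparent. The claim and the procedure meant to support it do not match.

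**Step 2: whether that person measures PT.** The article uses three descriptions: a data collection researcher (Blinding), a trained assessor (2.6.2.2) and one researcher who tests PT (2.10). It never equates them. PT is data collected directly before and after each session, so the overlap is likely, but it remains an inference.

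**Step 3: what the assessor meets after the session.** In A and B the probe is applied to an abdomen that has just had needles and 30 minutes of current. In C and D the abdomen has had neither. The article describes no covering of sites. Anyone testing PT at that moment may see where the needles were, even with earlier separation.

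**Step 4: how many readings are involved.**
- Sessions per patient: 14 (Interventions). PT time points per session: 2 (2.6.2.2).
- Total: 14 × 2 = 28 per patient.
- Immediately post-session: 14 of 28, or 50%. These carry any acute local effect in A and B.
- Pre-session: 14. One precedes all treatment. The other 14 − 1 = 13 come before a session in a twice-weekly schedule, so they fall days after the previous needling.
- At the planned 36 per group, A and B together hold 2 × 36 = 72 patients, giving 72 × 14 = 1,008 post-session readings on a freshly needled abdomen. C and D give the same number on an abdomen that was not needled.

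**Step 5: which contrasts are touched.**
- A/B versus C/D: affected, because needling of the tested region differs.
- A versus B, and C versus D: needle location is the same within each pair, and nothing in the text shows that blinding to intensity fails.
- VAS: rated by the patient for the previous week, with no probe and no assessor judgement.

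**The case against.** The strongest reply is that the article asserts blinding of assessment twice and nowhere says that anyone but the acupuncturist watches the needles go in. The start of treatment is not defined as a moment after insertion. Section 2.11, Data management and monitoring, speaks of two blinded data collection staff who handle the case report forms, so the data collector and the PT assessor could be different people. This stands as a limit: a reader might infer that the assessor is definitely unblinded, and the document does not establish that. It shows only that the stated procedure does not secure the blinding claimed.

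A second reply is that homotopic stimulation is expected to act locally through segmental inhibition, so a local change in threshold is partly the effect under study. This is also right. Not every local change is artefact, but an immediate reading on the needled region cannot tell the two apart.

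A third reply is that later pre-session readings come days after the last needling. This is accepted for acute local effects, and it is why those readings form part of the remedy.

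A reader might further infer that the tender point is chosen afresh at each test and so moves as pain improves. Section 2.6.2.2 does not say whether the point is re-chosen or kept, and an article may leave that to the full protocol. Re-selection would in any case tend to dilute a difference rather than create one. Fixing the point most tender at baseline would also bring regression to the mean into the planned before–after paired t tests. No change to the test point is asked for here.

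**Conclusion.** The point holds for the location contrast on one secondary outcome. Two conclusions should be kept apart.

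- **Blinding to location is not secured as written.** As far as it concerns the separation rule, this rests on the assumption that the PT assessor is the data collection researcher. The possibility that needle traces are visible at the post-session test adds to it, but that too is inferred.
- **The 14 post-session readings per patient combine segmental analgesia with local needling effects in A and B only.** This follows from the stated sites and timing, whoever the assessor is.

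The direction and size of any resulting bias cannot be worked out from the document. Local soreness would lower the threshold and numbness would raise it. A false-positive rate could be obtained only by assuming a shift, and would merely restate that assumption. A reader might also extend the problem to the whole trial; the text does not support that, since the intensity contrasts and the patient-rated VAS are not shown to be affected.

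**What to change.** 1. **Blinding.** Amend the section so that the data collector and the PT assessor leave before needle insertion and return only after the needles are out. State whether they are the same person.
2. **Masking.** Cover the abdominal and leg acupoint sites identically in every patient, whatever the group, with small dressings that leave the PT test point accessible to the probe.
3. **Analysis.** Base the between-location PT comparison on pre-session readings, before session 14 versus before session 1. Report immediate post-session PT as a descriptive acute measure.

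The cost is protocol wording and dressings, with no added visits or measurements. There are three drawbacks. Acute PT loses its inferential role. The reading before session 14 reflects 13 of the 14 sessions. The Trial status section says recruitment is under way, so the masking change applies only from the amendment onward. The pre-session analysis can use all patients, but in those treated before the amendment it removes the acute local effect without removing any knowledge of location the assessor may already have gained. The report should therefore state how many patients were treated before and after the change.

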### Interventions

All EA treatments will be performed by one acupuncturist who has more than 10 years of experience and a Chinese medicine practitioner license. The treatments will be performed according to the standard protocol already prepared. All participants will take a supine position on the treatment couch to receive treatment. Each participant will receive 14 sessions of treatments, twice a week for 7 weeks. Each session will last for 30 min. No additional treatment is allowed.

All selected patients will be randomized to four groups: group A will receive EA at homotopic acupoints with noxious current intensity, which will be 30% above the patient’s pain threshold. Group B will receive EA at homotopic acupoints with innocuous current intensity, which will be 30% below the patient’s pain threshold. Group C will receive EA at heterotopic acupoints with noxious current intensity. Group D will receive EA at heterotopic acupoints with innocuous current intensity. Thus, group A is called the homotopic noxious group, group B is called the homotopic innocuous group, group C is called the heterotopic noxious group, and group D is called the heterotopic innocuous group. We selected the homotopic acupoints ST25 (Tianshu) and ST26 (Wailing), and the heterotopic acupoints ST36 (Zusanli) and ST37 (Shangjuxu), because these acupoints are most commonly used to treat IBS in China [20].

After local area disinfection, sterile, disposable needles (length 50 mm, diameter 0.30 mm; Huatuo, Suzhou Medical Supply Factory Co., Ltd., Suzhou, China) will be inserted to a depth of 25–40 mm. The acupuncturist will manipulate the needle to achieve a “De-qi” sensation for the patient. ST25 will be connected to the same-side ST26 in group A and group B. ST36 will be connected to the same-side ST37 in group C and group D. The reason behind the connection is to form a circuit containing a HANS-200E stimulator (Nanjing Jisheng Co., China) for 30 min. The frequency in all four groups will be the same as an alternating wave with a frequency of 2/100 Hz. The treatment details for the four groups are presented in Table 1.

**Table 1 Tab1:** Details of treatment in the four groups

Group	Points	Stimulation parameters
Group A	Tianshu (ST25) Wailing (ST26)	Current intensity is 30% above the patient’s pain threshold. Alternating wave with a frequency of 2/100 Hz
Group B	Tianshu (ST25) Wailing (ST26)	Current intensity is 30% below the patient’s pain threshold. Alternating wave with a frequency of 2/100 Hz
Group C	Zusanli (ST36) Shangjuxu (ST37)	Current intensity is 30% above the patient’s pain threshold. Alternating wave with a frequency of 2/100 Hz
Group D	Zusanli (ST36) Shangjuxu (ST37)	Current intensity is 30% below the patient’s pain threshold. Alternating wave with a frequency of 2/100 Hz

### Outcome assessments

#### Primary outcome measurement

##### 2.6.1.1. Abdominal pain intensity (0–100 mm visual analog scale (VAS))

Each patient will rate her abdominal pain from the previous week on a 0–100 mm scale, with 0 indicating no pain and 100 the worst imaginable pain. According to a previous study [21], the reliability and validity of the VAS in patients with IBS has been established.

##### 2.6.1.2. IBS Symptom Severity Scale (IBS-SSS)

This questionnaire consists of five questions summing to a score of 500 points. The five questions concern abdominal pain intensity, abdominal pain frequency, abdominal distension degree, defecation satisfaction, and interference with quality of life. SSS intensity is assessed by the total score. If the score is lower than 75, the patient is considered to be in remission. When the score is 75–175, 175–300, and above 300, we will consider the patient to be mild, moderate, and severe, respectively. The reliability and validity of the IBS-SSS for treatment has been verified in many studies [22, 23].

##### 2.6.2.2. Pain threshold (PT)

PT is a secondary outcome in this study, and is a more objective measure of pain than the VAS. The PT will be tested by a digital algometer (EP601C, East China Normal University of Science and Technology, Guangxi, China) immediately before and after each treatment. The most obviously tender point (Ashi point) on the abdomen will be tested. The patient will lie in a supine position on the treatment couch. The algometer has a 1-cm^2^ rubber probe, which will be pressed vertically against the abdominal wall. The trained assessor will position the algometer perpendicular to the tender point and apply gradual pressure at a steady rate of approximately 0.5 kg/cm^2^/s. The patient will request the treatment to be stopped when the applied pressure becomes painful, and the value on the digital algometer will be recorded. The pressure pain threshold will be measured three times at each point, with the average value collected for analysis.

##### 2.6.2.3. The Symptom Checklist-90 (SCL-90)

Psychological status will be assessed by the SCL-90 [25], which comprises 10 symptom factors: somatization, obsessive-compulsive disorder, interpersonal sensitivity, depression, anxiety, hostility, phobic anxiety, paranoid ideation, psychoticism, and other. The sum of the 10 component scores will be the final score. Higher scores indicate poorer mental status.

### Follow-up

All participants will be asked to return in 3 months for follow-up. The researcher will contact participants via telephone to collect therapeutic effect information after the treatment has been completed for 3 months.

#### 2.8. Sample size

The trial aims to detect a difference in analgesic effect between the four parallel groups. There are insufficient previous data regarding VAS scores for the treatment of IBS using EA. Therefore, we could not calculate the appropriate sample size according to the sample size calculation formula. We plan to enroll 144 patients, with 36 individuals in each group, allowing for 20% attrition. The outcomes of this pilot study will aid in the calculation of the appropriate sample size for further randomized clinical trials.

#### 2.9. Adverse events

All patients will be asked to report any adverse events during the trial. Possible adverse events include local pain, bleeding, local infection, palpitations, fainting, and other symptoms. The researcher will address and record all adverse events. Once a serious adverse event occurs, the researcher may need to terminate the trial and submit a written report to the Research Ethics Committee immediately.

### 2.10. Quality control

To guarantee the quality of this study, we will run several simulations with our colleagues playing the role of patients to identify any problems with our study protocol before the study begins. The one researcher who tests the PT will be trained many times to improve consistency of results. To guarantee the objectivity of the data, effect assessment and statistics will be blinded during the study period. Finally, all details will be recorded on a patient case report form (CRF).

#### 2.11. Data management and monitoring

All patient data will be recorded on the CRF at each visit. Two blinded data collection staff will collect the CRFs and perform double-data entry. A qualified clinical trial expert will monitor the entire process of this RCT. The Clinical Research Center of Guangdong Hospital of Traditional Chinese Medicine will check the CRFs periodically to ensure the quality and timeliness of data.

### 2.11. Statistical analyses

The statistical analyses will be performed by a statistician who will be blinded to the treatments and study protocol. All data will be analyzed according to intention-to-treat (ITT) principles to reduce deviation. Non-continuous variables will be analyzed by chi-square test. All normally distributed continuous variables will be described by mean ± standard error (SEM). The paired *t* test will be used to compare the outcome measurements before and after treatment. The differences between group and time will be analyzed by repeated measures analysis of variance (ANOVA). If we find a significant overall difference among the four groups for a particular outcome, we will use the post hoc test (Newman-Keuls test) to adjust for multiple comparisons to determine the statistical differences among pairwise groups. All analyses will be conducted with SPSS (version 21.0) software. A *P* value of 0.05 or less will be considered statistically significant.

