**Discussion:**

The aim of this study is to assess the analgesic effect of EA at homotopic (abdomen) acupoints and heterotopic (lower limb) acupoints on abdominal pain in patients with IBS, as well as the difference in analgesic effects between noxious and innocuous stimulation.

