## Methods/design

### Study design

This study is a single-blind randomized controlled trial (RCT) that aims to compare the analgesic effect of two homotopic acupoint groups (noxious intensity and innocuous intensity) and two heterotopic acupoint groups (noxious intensity and innocuous intensity) for IBS. A total of 144 female patients will be recruited from the Guangdong Provincial Hospital of Traditional Chinese Medicine. Patients will be randomized to the homotopic noxious stimulation group (group A), the homotopic innocuous stimulation group (group B), the heterotopic noxious stimulation group (group C), or the heterotopic innocuous stimulation group (group D) in a 1:1:1:1 ratio. Patients will receive 14 sessions of EA treatment twice a week for 7 weeks. Each session will last 30 min. The flowchart of the trial is shown in Fig. 1. The study schedule is detailed in Fig. 2. The Standard Protocol Items: Recommendations for Interventional Trials (SPIRIT) checklist is provided as Additional file 1.

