### Participants

#### Inclusion criteria

Patients who meet the following criteria are eligible for inclusion in the study: (1) they are females aged between 18 and 50 years, (2) they meet the criteria for IBS according to the Rome III diagnostic criteria, (3) IBS has been their main complaint for at least 6 months, (4) their average abdominal pain score has been greater than 30 mm (on a scale of 0–100 mm, with 0 indicating no pain and 100 the worst imaginable pain) in the past 2 weeks, and (5) they have signed an informed consent form.

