## Discussion

At present, the most well-known clinical application of acupuncture in the world is for chronic pain. However, many specific questions about the therapeutic effect of acupuncture also exist. It is generally believed that multifaceted factors influence its curative effect, among which acupoint selection is vital. It is well known that each point has its particular therapeutic indication, and acupuncture at different acupoints shows different effects. Therefore, more trials are needed to investigate differences in acupoint selection. Most studies on acupoint selection have focused on traditional Chinese medicine (TCM) theory or the treatment effects of acupuncture. However, few studies have used DNIC to select the appropriate points and optimal EA intensity for clinical practice.

DNIC in patients with IBS has been shown to be decreased compared to healthy controls. A high-quality study showed that patients with IBS failed to show pain suppression during a DNIC session and showed little decrease in pain [18]. In a similar finding, heterotopic acupoint stimulation cannot induce significant acupuncture analgesia. At this point, EA may not be effective. Therefore, we hypothesize that homotopic acupoints (ST25 and ST26) will have better effects than heterotopic acupoints (ST36 and ST37). The real result will help guide us in choosing effective acupoints (homotopic or heterotopic acupoints) to treat abdominal pain.

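### With four active EA arms and no sham or untreated arm, neither the before-after paired t tests nor the ANOVA time effect can show that EA at a site relieves pain; only the between-arm contrasts are protected by randomisation

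*Protocol article*

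**What the plan says.** Under Statistical analyses (2.11), a paired t "test will be used to compare the outcome measurements before and after treatment". The same paragraph plans a repeated measures ANOVA for group and time, followed by Newman-Keuls pairwise tests if the overall group difference is significant. It closes with one rule for everything: a P "value of 0.05 or less will be considered statistically significant". Nothing marks the paired tests as descriptive.

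Study design describes a comparison of "two homotopic acupoint groups (noxious intensity and innocuous intensity) and two heterotopic acupoint groups (noxious intensity and innocuous intensity) for IBS", randomised "in a 1:1:1:1 ratio". Interventions and Table 1 confirm that every arm gets active EA at one of two sites and one of two intensities.

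Inclusion criterion 4 requires that "their average abdominal pain score has been greater than 30 mm" over the past 2 weeks on a 0-100 mm scale. The primary outcome is a rating of the previous week's abdominal pain on the same scale.

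The aim is worded in two ways. The Discussion part of the Abstract wants to "assess the analgesic effect of EA at homotopic (abdomen) acupoints and heterotopic (lower limb) acupoints on abdominal pain", and also to assess the difference between intensities; the end of the Background is similar. Study design and Sample size (2.8) instead speak of comparing, or detecting a difference between, the four groups.

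**The concern.** A significant fall within an arm is easily read as evidence that EA at that site works. Here such a fall has at least three other explanations. IBS pain fluctuates over 7 weeks of treatment; patients who know they are being needled expect relief; and patients selected for pain above a cut-off tend to score lower next time. A sham or untreated arm would absorb all three, and there is none.

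A second misuse is possible. A significant change in one arm and a non-significant one in another is not a test of the difference between them. At stake are absolute statements, that EA reduced pain or that one site does nothing, which this design cannot support. The relative question is not at stake.

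**Working it through.** **Inputs from the protocol.** Four arms of 36, 4 × 36 = 144, which matches the stated total. Attrition of 20%: 36 × 0.8 = 28.8, about 29 evaluable per arm. Entry above 30 mm. Level 0.05; sidedness is not stated, so two-sided is assumed. Sample size (2.8) gives no SD, effect size or power.

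**Assumed, not in the documents.** SD 20 mm; unselected mean μ of 30, 40 or 50 mm; test-retest correlation ρ of 0.5, 0.7 or 0.8; no treatment effect. A result counts only if it is significant in the direction of improvement, so the nominal rate is 2.5%.

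**Expected fall when the baseline is the entry score.** Fall = SD × λ × (1 − ρ), with λ = φ(z)/(1 − Φ(z)) and z = (30 − μ)/SD.
- μ = 40, ρ = 0.7: z = −0.5, λ = 0.3521/0.6915 = 0.509; 20 × 0.509 × 0.3 = 3.05 mm (simulated 3.06).
- Largest, μ = 30, ρ = 0.5: λ = 0.3989/0.5 = 0.798; 20 × 0.798 × 0.5 = 7.98 mm (simulated 7.85 with scores clipped to 0-100).
- Smallest, μ = 50, ρ = 0.8: λ = 0.2420/0.8413 = 0.288; 20 × 0.288 × 0.2 = 1.15 mm (simulated 1.16).

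**What the paired t test makes of it.** For μ = 40, ρ = 0.7 the simulated SD of change is 14.84 mm. The standard error is 14.84/√36 = 2.47, and the expected t is 3.05/2.47 = 1.24 against a critical 2.03. A normal approximation gives 1 − Φ(2.03 − 1.24) = 0.21; simulation gives 0.224. For at least one of four arms, 1 − (1 − 0.224)⁴ = 0.64, and simulation gives 0.640. Two identical arms would split, one significant and one not, with probability 2 × 0.224 × 0.776 = 0.35.

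**The time effect has the same weakness.** Pooling 144 patients in one before-after contrast shrinks the standard error to 14.84/√144 = 1.24 while the fall stays at 3.05 mm. The expected t is 3.05/1.24 = 2.5, with a critical value near 1.98 and a probability of about 1 − Φ(1.98 − 2.5) = 0.7.

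**Range over all assumed values (simulation).**

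| Baseline VAS | Mean fall, mm | One arm, n = 36 | One arm, n = 29 | At least one of four, n = 36 |
|---|---|---|---|---|
| Same as entry score | 1.2 to 7.8 | 8-72% | 7-61% | 28-99% |
| Last week of the two-week average | 0.6 to 4.5 | 4-29% | 4-23% | 16-74% |
| Separate measurement | about 0 | about 2.5% | about 2.5% | 9-10% |

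The last entry is what chance alone gives: 1 − 0.975⁴ = 9.6%.

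**Between-arm contrast.** The expected fall from selection is the same in every randomised arm, so in the example the expected difference is 3.05 − 3.05 = 0. This follows from randomisation and was not simulated.

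Natural course and expectation cannot be sized from the documents. They would add to any within-arm change in all three rows.

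**The case against.** The strongest reply is that the plan never ties an efficacy claim to the paired tests. It says only what they compare, it already provides a direct between-arm analysis, and most of the article frames the question as relative: Study design, Sample size, and the Discussion's hypothesis that homotopic points do better. All of that stands, and it confines the point to absolute statements.

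Three stronger readings are tempting and should not be drawn.
- A reader might infer that the paired tests are the plan's chosen means of judging efficacy. That comes from joining the aim in the Abstract to the analysis section; the article does not say it. Nor are they the only before-after analysis, since the ANOVA includes time.
- A reader might infer from the Discussion's remark that "heterotopic acupoint stimulation cannot induce significant acupuncture analgesia" that a non-significant arm will be declared ineffective. In context the sentence is background leading to a relative hypothesis. It sets no decision rule.
- A reader might infer that arms will look effective through regression to the mean alone. That depends on how the baseline is taken. Entry uses a two-week average at a screening interview; the VAS covers the previous week and is rated before the first treatment. The interval between them is not stated. If the two are separate, the threshold-driven excess disappears.

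It can also be said that baseline adjustment and descriptive labelling belong in an analysis plan that is not shown, and that Sample size calls this a pilot. That lowers the weight of the point. It does not remove it, because the article itself fixes the test, the significance rule and the wording of the aim.

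**Conclusion.** The point holds for absolute claims only. A significant within-arm P value, or a significant time effect, cannot be attributed to EA in a trial where every arm is treated, yet part of the aim is worded as though it could. The excess of significant improvements under no effect ranges from none (separate baseline, 2.5% per arm) through 4-29% (partial overlap) to 8-72% (baseline equal to the entry score). These ranges rest on assumed SD, mean and correlation, because the protocol supplies none of them. Even in the most favourable case, natural course and expectation remain uncontrolled. The comparison of sites and intensities between randomised arms is not biased by this.

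**What to change.** 1. In Statistical analyses, replace the paired t tests with a descriptive report of within-arm change: mean change with 95% confidence interval and no significance claim. Treat the ANOVA time effect in the same way.
2. Base all conclusions on between-arm differences adjusted for the baseline value already collected.
3. In the Abstract and at the end of the Background, reword the aim to match Study design and Sample size: homotopic versus heterotopic, and noxious versus innocuous stimulation.

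The cost is wording and fewer tests. No patients, arms or visits are added. The price is that the trial gives up any statement that EA at a given site is effective in itself.
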